# Efficacy, safety and cost-effectiveness of methotrexate, adalimumab or their combination in non-infectious non-anterior uveitis: a protocol for a multicentre, randomised, parallel three arms, active-controlled, phase III open label with blinded outcome assessment study

**DOI:** 10.1136/bmjopen-2021-051378

**Published:** 2022-03-22

**Keywords:** clinical trials, ophthalmology, rheumatology

## Abstract

**Introduction:**

Non-infectious uveitis include a heterogeneous group of sight-threatening and incapacitating conditions. Their correct management sometimes requires the use of immunosuppressive drugs (ISDs), prescribed in monotherapy or in combination. Several observational studies showed that the use of ISDs in combination could be more effective than and as safe as their use in monotherapy. However, a direct comparison between these two treatment strategies has not been carried out yet.

**Methods and analysis:**

The Combination THerapy with mEthotrexate and adalImumAb for uveitis (CoTHEIA) study is a phase III, multicentre, prospective, randomised, single-blinded with masked outcome assessment, parallel three arms with 1:1:1 allocation, active-controlled, superiority study design, comparing the efficacy, safety and cost-effectiveness of methotrexate, adalimumab or their combination in non-infectious non-anterior uveitis. We aim to recruit 192 subjects. The duration of the treatment and follow-up will last up to 52 weeks, plus 70 days follow-up with no treatment. The complete and maintained resolution of the ocular inflammation will be assessed by masked evaluators (primary outcome). In addition to other secondary measurements of efficacy (quality of life, visual acuity and costs) and safety, we will identify subjects’ subgroups with different treatment responses by developing prediction models based on machine learning techniques using genetic and proteomic biomarkers.

**Ethics and dissemination:**

The protocol, annexes and informed consent forms were approved by the Reference Clinical Research Ethic Committee at the Hospital Clínico San Carlos (Madrid, Spain) and the Spanish Agency for Medicines and Health Products. We will elaborate a dissemination plan including production of materials adapted to several formats to communicate the clinical trial progress and findings to a broad group of stakeholders. The promoter will be the only access to the participant-level data, although it can be shared within the legal situation.

**Trial registration number:**

2020-000130-18; NCT04798755.

Strengths and Limitations of this StudyThis is the first randomised controlled study designed to compare the efficacy of combination therapy versus monotherapy for the treatment of non-infectious uveitis in subjects with no previous immunosuppressive treatment.We have chosen quite a strict outcome (the requirement of a maintained controlled inflammation), more likely related to long-term outcomes (such as structural damage) and to patient-reported outcome measures.Despite the previous point, our primary efficacy outcome is still a surrogate marker: the achievement of this outcome does not have necessarily to translate in an improvement of outcomes more important for the patient, such as quality of life or disability.The requirement to control the inflammatory process early (by week 16) may cause an underestimation of drug efficacy, as it could take more time to control the inflammation but be associated with a similar long-term prognosis.The lack of masking could introduce bias, although treatment characteristics and proven effectivity in non-infectious uveitis, the duration of the trial (up to 52 weeks) and the need for biweekly subcutaneous injections of one of the drugs (adalimumab), we consider unpractical for the subject the use of placebo in the present trial.

## Introduction

Uveitides are potentially sight-threatening diseases:^1^ worldwide, they represented up to 10% of causes of blindness (almost 4 million people).^2^ Furthermore, in the European Union and the USA, after diabetic retinopathy, uveitides represent the second major treatable cause of blindness in those 20–65 years of age^3^ (up to 10% of cases of blind registrations^3–6^). Additionally, a high percentage of patients suffer from uveitis-related complications, visual impairment^4 7 8^ and a negative impact in quality-of-life (QoL).^9 10^ Considering their higher prevalence in young to middle-aged adults,^11 12^ uveitides cause an important economic, social and personal burden.^5 13–16^

The correct management of non-infectious uveitis (NIUs) is essential for preserving visual function and avoiding ocular and extra-ocular morbidity.^17^ Although glucocorticoids (GCs) are the mainstay of treatment,^18^ under certain circumstances, adding immunosuppressive drugs (ISDs) is needed to achieve a sustained control of the inflammatory process.^19^ Several ISDs are used in the standard of care, such as methotrexate (MTX) and biological agents.^19–21^

Regarding MTX, its effectiveness in NIU has been assessed in two randomised clinical trials, compared with mycophenolate mofetil (MMF): Rathinam *et al*
22 observed that 69% and 47% of patients treated with MTX and MMF, respectively, achieved complete control of inflammation and daily oral GCs dosage ≤10 mg at 5 and 6 months (p=0.09). In a second trial,^23^ randomising 200 patients, the percentage of subjects achieving a similar outcome was 67% and 57% for MTX and MMF, respectively (p>0.05), with similar tolerability. Regarding safety, adverse events (AEs) are generally mild and discontinuations due to serious adverse events (SAEs) are less common than for most ISDs,^24 25^ translating it in higher retention rates.^26 27^

Regarding adalimumab (ADA), its effectiveness in NIU has been shown in two randomised controlled trials.^28 29^ The VISUAL I study^28^ compared ADA with placebo in 217 NIU patients with active uveitis despite ≥10 mg/day of systemic GCs. Based on the cumulative number of subjects with treatment failure in each visit, by week 25 (about 6 months), 31 of 107 (29%) subjects in the placebo group and 62 of 110 (56%) subjects in the ADA group had not suffered a treatment failure. By 50 weeks, the numbers were reduced to 24 (22%) and 51 (46%), respectively. Regarding safety, many of the AEs are sufficiently mild to not require discontinuation, such as injection site pain and antidrug antibodies formation,^19 30 31^ reflecting in a high retention rate.^32^ Regarding SAEs, there was no association with higher risk in a recent meta-analysis,^33^ compared with placebo or synthetic ISDs. However, ADA was associated with a higher risk of treatment discontinuation due to SAEs. One of the most important ADA’s AEs are infections. However, a previous meta-analysis reported that the absolute risk was low (0.036% with TNF-alpha inhibitors vs 0.017% with placebo),^34^ which probably does not represent a clinically important constraint on the use of these agents. Finally, ADA has not showed an association with a higher risk of malignancy.^33^

Although ISDs are usually used in monotherapy in uveitis, several observational studies have shown that in 21%–52% of NIU patients, the use of ISDs in monotherapy was unable to achieve a sustained control of the inflammatory process.^27 35–37^ Furthermore, other studies have provided evidence that the combination of two or more ISDs could offer advantages in terms of effectiveness and tolerability,^38–41^ in conditions such as Birdshot retinochoroidopathy,^38^ serpiginous choroiditis,^39 40^ Vogt-Koyanagi-Harada syndrome (VHK),^42 43^ ocular Behçet’s disease,^44 45^ JIA associated uveitis,^46^ sympathetic ophthalmia^47^ and intermediate uveitis.^48^ Regarding the beneficial of combining both MTX and ADA, several RCTs have provided evidence in other immune-mediated inflammatory diseases (IMIDs).^49^ In NIU, this combination was tested in children with Juvenile Idiopathic Arthritis-associated Uveitis and a previous failure to MTX monotherapy.^50^ The combination of MTX and ADA was more effective compared with MTX and placebo, although it was associated with a higher proportion of AEs (88% vs 83% of patients) and SAEs (22% vs 7%).

Despite all the evidence, a direct comparison between combination and monotherapy has not been tested yet, although some groups have adopted the use of combination therapy as the initial ISD treatment for particular conditions.^51^

There are currently no tools able to predict the response or non-response to ISDs in those NIUs needing immunosuppression, as there is marked interpersonal variation in their efficacy and toxicity. Response to the first-line ISD treatment could be an important predictor of long-term outcomes, as the continuous or repeated eye inflammation could increase the risk of structural permanent damage, leading to blindness, disability and deterioration in the QoL. Therefore, starting on the right ISD is likely a key factor in achieving a better and more cost-effective therapy, and improving the optimal allocation of healthcare resources. To achieve these aims, objectively measured and evaluated characteristics (biomarkers^52^) are required, in addition to the identification of clinical features associated with the outcomes of interest.

## Methods and analysis

### Study overview

The Combination THerapy with mEthotrexate and adalImumAb for uveitis (CoTHEIA) study is a phase III, multicentre, prospective, randomised, single-blinded with masked outcome assessment, parallel three arms with 1:1:1 allocation, active-controlled, superiority study design, comparing the efficacy, safety and cost-effectiveness of MTX, ADA or their combination in non-infectious non-anterior uveitis. The duration of the treatment and follow-up will last up to 52 weeks. A 70-day follow-up clinic visit or phone call will take place to assess safety after the last study drug dose. Figure 1 provides an overview of the study timeline and interventions.

**Figure 1 F1:**
[figure not shown]
Overview of the study timeline and interventions. ADA, adalimumab; MTX, methotrexate.

### Objectives and outcome variables

The trial main hypothesis is that the use of combination therapy with MTX and ADA will be more effective in inducing and maintaining ocular inflammatory inactivity than either drug given in monotherapy.

The *primary efficacy objective* is to establish which treatment strategy results in a higher proportion of subjects achieving a complete and maintained resolution of the ocular inflammation, on an intent to treat basis. The *primary efficacy outcome* will be the proportion of patients achieving a *Good Clinical Response* between the combination therapy arm and the single ISD arms. This outcome is defined as a complete resolution of the ocular inflammatory signs (including active chorioretinal lesions, active retinal vascular inflammation, uveitis macular oedema, presence of anterior chamber cells and presence of vitreous haze), achieved within the first 16 weeks of the study and maintained during follow-up until the end of the study (week 52); furthermore, there must not be a treatment failure due to safety or intolerability; the subject must adhere to the initial (up to week 16) oral GCs tapering protocol; all study visits from baseline to 16 weeks must be completed and at the final visit (week 52), the subject must be treated with up to 7.5 mg/day of oral prednisone (or equivalent) and up to two times a day of prednisolone acetate 1% (or equivalent). The *secondary efficacy objectives* and outcomes variables can be found at table 1.

**Table 1 T1:** Efficacy-related secondary objectives and outcome variables

Objective	Outcome variable
To compare the fraction of subjects who achieve a complete inflammatory ocular inactivity by week 16	Complete abrogation of the ocular inflammatory signs, which is achieved within the first 16 weeks of the study, no treatment failure due to safety or intolerability; compliance with the initial (up to week 16) oral GCs tapering protocol, and completion of all study visits from baseline to 16 weeks
To compare several Patient-Reported Outcomes Measures (health-related and vision-related quality of life, anxiety and depression) between treatment strategies	EuroQuol 5D-5L Visual Functioning Questionnaire-25 Hospital Anxiety and Depression Scale
To compare the presence of the clinical components of the Good Clinical Response variable between treatment strategies during follow-up	Active chorioretinal lesions; active retinal vascular inflammation; macular oedema; ACC; vitreous haze and loss of CVA secondary to inflammation at baseline, week 16, week 52 and relapse visit
To compare the time to relapse after week 16 between treatment strategies	The time to inflammatory relapse between groups, defined as the time from visit 16 weeks until end of the study, loss of follow-up or appearance of at least one ocular inflammatory manifestation, in those individuals achieving a Good Clinical Response by visit 16 week
To compare the evolution of visual acuity during follow-up	Best-corrected visual acuity (BCVA) during follow-up
To compare the development of anti-adalimumab antibodies during the follow-up, between those subjects treated with monotherapy and combination therapy	Assessment of anti-ADA antibodies (AAA) at week 15, 27, 51 and relapse
To assess the cost-utility and cost-effectiveness from both a Health System and a Societal perspective of the combination therapy and the ADA monotherapy compared with MTX given alone	Direct and indirect cost, and incremental cost effectiveness ratios. Drug costs will be calculated individually for each patient taking as reference the price published in 2022 by the Health Ministry for the Spanish Health System. Outpatient and inpatient care, other medical cost, home care and productivity loss will be estimated based on the data from eSalud database^68^ and from the Minimum Basic Data Set of the Spanish Health Ministry.^69^

ADA, adalimumab; GC, glucocorticoid; MTX, methotrexate.

Security-related objective will establish which treatment strategy has better tolerability. Safety outcomes will be collected in the form of AEs, physical examination and laboratory tests throughout the treatment period and up to 70 days after the last dose in this study. Gender of the subjects will be taken into account.^53^

*Pharmacogenetic and proteomic-related objectives* include identifying groups of subjects more likely to respond to the different treatment strategies, using genetic and proteomic biomarkers. For the former, subjects will be genotyped for known and validated genetics single nucleotide polymorphisms (SNPs) associated with a MTX^54^ and ADA^55^ response in different IMIDs. For the latter, a Discovery (shotgun proteomic analysis), Verification (targeted proteomics using multiple reaction monitoring (MRM) test) and Validation (antibody-based microarrays absolute quantification tests) phases will be carried out, following optimised protocols and procedures.^56–61^

Finally, a *Biobank substudy-related objective* will be carried out with the aim of boosting the translational research in the field of NIUs, by creating a collection of blood-derived samples (serum, plasma, total blood RNA and DNA) from the participant subjects in order to advance in the identification and validation of biomarkers associated with treatment response or deepen in the pathophysiology of these conditions.

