### Authorised rescue medication

During whole study up to two inflammatory relapses (unilateral or bilateral) will be allowed, one during the first period (baseline–week 16: ACC relapse) and one during the second period (week 16–week 52: any location), before declaring the lack of response to the assigned medication. Based on the location and severity of the relapse, a protocolised rescue treatment with Topical AND/OR Local OR Oral GCs will be allowed. In case inflammation cannot be suppressed in 4 weeks, or a new relapse takes place after 4 weeks, it will be declared treatment failure and the subject will exit the study.

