### Study procedures

Study visits will be the baseline visit, visits at weeks 1, 4, and every 4 weeks thereafter until (a) the subject is determined as unable to achieve complete resolution of the ocular inflammatory process by week 16, OR; (b) the subject is determined as unable to maintain a complete resolution of the ocular inflammatory process, between weeks 16 and 52 OR; (c) the subject completes 52 weeks of this clinical trial, OR; (d) the study is stopped due to the findings of the Data Security Monitoring Board, OR and (e) the subject meets any of the study finalisation criteria.

Informed consent has to be acquired before carrying out any study procedure, including screening tests (online supplemental file 1 contains a sample informed consent). Before baseline (when the subject is randomised), several screening visits can take place up to 14 days before that visit, in order to obtain all the required complementary tests to assess eligibility. The visit window for all scheduled visits is ±3 days through week 4 and ±7 days for all visits following the week 4 study visit. Table 3 provides an overview of the study activities.

10.1136/bmjopen-2021-051378.supp1Supplementary data

**Table 3 T3:** Study activities

Activity	Screening	Baseline	w1	w4	w8	w12	w16	w20	w24	w28	w32	w36	w40	w44	w48	FET	Relapse	Unsch.	70-day follow-up
Informed consent	X																		
Inclusion/exclusion criteria	X	X																	
Medical/surgical history	X	X																	
History of tobacco and alcohol use	X	X																	
Uveitis history	X	X																	
Vital signs/weight/height	X	X														X	(X)		
Physical exam	X	X														X	(X)		
Symptom directed physical exam			X	X	X	X	X	X	X	X	X	X	X	X	X		X		
Chest X-ray	X															X*			
Cerebral MRI†	(X)																		
TB screening	X																		
Serum pregnancy test††	X	X	X	X	X	X	X	X	X	X	X	X	X	X	X	X			
Hepatitis B/C screening	X																		
Syphilis testing (FTA)	X																		
Randomisation		X																	
Best-corrected visual acuity testing	(X)‡	(X)‡		X	X	X	X	X	X	X	X	X	X	X	X	X	X		
Tonometry	(X)‡	(X)‡		X	X	X	X	X	X	X	X	X	X	X	X	X	X		
Slit lamp exam	(X)‡	(X)‡		X	X	X	X	X	X	X	X	X	X	X	X	X	X		
Dilated indirect ophthalmoscopy	(X)‡	(X)‡		X	X	X	X	X	X	X	X	X	X	X	X	X	X		
Fundus photography	(X)‡	(X)‡					X									X	X		
Optical coherence tomography	(X)‡	(X)‡		X	X	X	X	X	X	X	X	X	X	X	X	X	X		
EuroQol-5D	(X)‡	(X)‡		X	X	X	X	X	X	X	X	X	X	X	X	X	X		

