#### Planned methods of statistical analysis for efficacy-related objectives

The primary analysis will be a Mantel–Haenszel test (MHT), stratified by NIU location, comparing the combination therapy arm and the single ISDs arms (both arms combined), and performed in the ITT set. Achievement of the Good Clinical response will be considered the binary response variable: those subjects achieving a Good Clinical versus those not achieving the outcome (regardless the cause). The exposure variables will be the treatment arm: those subjects receiving combination therapy versus those receiving either monotherapy. Uveitis location will be the strata: intermediate uveitis versus posterior OR panuveitis. If the results of the primary analysis are significant, then pairwise comparisons using MHT stratified by NIU location will be carried out. P values of the pairwise comparisons will be adjusted using the Bonferroni method. No interim efficacy-related analysis will be carried out.

Secondary efficacy-related analyses are designed to test the hypothesis that treatment assignment affects a given outcome, after controlling for selected covariates. Details can be found at table 4.

**Table 4 T4:** Planned methods of statistical analysis for efficacy-related secondary outcomes

Outcome variable	Statistical analysis
Complete abrogation of the ocular inflammatory signs, which is achieved within the first 16 weeks of the study, no treatment failure due to safety or intolerability; compliance with the initial (up to week 16) oral GCs tapering protocol and completion of all study visits from baseline to 16 weeks	MHT, stratified by NIU location. If p-value<0.05, pairwise comparisons using MHT stratified by NIU location will be carried out with Bonferroni adjustment of the pairwise p-values
EQ5D	GEE models nested by patient^70 71^ and adjusted by study visit (continuous) and treatment arm (discrete) will be carried out, using a Gaussian family and Identity as link function. Different covariable structures will be tested (independent and exchangeable) and compared using the Bayesian Information Criteria. Time x study arm interactions will assess different effects of time in the evolution of the outcome by arm. P-value<0.05 will be considered as a significant interaction
Visual Functioning Questionnaire-25 Hospital Anxiety and Depression Scale	Changes between Baseline and w16, and the FET visit will be compared between treatment groups using ANOVA

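### The week-16 response outcome does not require quiet eyes at week 16, so some subjects inflamed at that visit score as successes

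*Protocol article*

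**What the plan says.** Under Objectives and outcome variables, Table 1 pairs the objective "To compare the fraction of subjects who achieve a complete inflammatory ocular inactivity by week 16" with an outcome that has four conditions. The first two are worded "Complete abrogation of the ocular inflammatory signs, which is achieved within the first 16 weeks of the study, no treatment failure due to safety or" (the second condition covers tolerability as well as safety). The other two are "compliance with the initial (up to week 16) oral GCs tapering protocol, and completion of all study visits from baseline to 16 weeks". Table 4 repeats the timing: "Complete abrogation of the ocular inflammatory signs, which is achieved within the first 16 weeks of the study".

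The primary outcome in the same section uses the same timing phrase but adds persistence: "achieved within the first 16 weeks of the study and maintained during follow-up until the end of the study (week 52").

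Three other parts bear on the point:
- Authorised rescue medication permits one relapse before week 16, "one during the first period (baseline–week 16: ACC relapse"). It then states: "In case inflammation cannot be suppressed in 4 weeks, or a new relapse takes place after 4 weeks, it will be declared treatment failure". Such a subject leaves the study.
- Study procedures ends visits when "the subject is determined as unable to achieve complete resolution of the ocular inflammatory process by week 16".
- The time-to-relapse outcome (Tables 1 and 4) starts its clock at the week-16 visit, in subjects with a Good Clinical Response by that visit.

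**The concern.** The primary outcome needs a second clause to express persistence. The week-16 outcome drops that clause and puts nothing in its place. Its only failure exclusion concerns safety and tolerability, so failure from inflammation is not named.

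Three things are at stake:
- The week-16 response rate may include subjects with active uveitis at week 16.
- If one arm's advantage lies in staying quiet rather than becoming quiet, the outcome partly hides it. The trial's main hypothesis covers both inducing and maintaining inactivity.
- Good Clinical Response as defined needs follow-up to week 52, so the week-16 outcome is the nearest available entry rule for the time-to-relapse analysis. Used literally, it admits eyes already inflamed, with an event at time zero.

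**Working it through.** **Reading the rule against the visit schedule.** Table 3 places slit-lamp examinations at weeks 4, 8, 12 and 16, with none at week 1. Take subjects who follow the taper and have no safety failure:

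| Record | Visits to week 16 completed | Literal score | State at week 16 |
|---|---|---|---|
| Active at 4 and 8, quiet at 12 and 16 | yes | success | quiet |
| Quiet at 4, 8 and 12, signs return at 16 (route a) | yes | success | inflamed |
| Quiet at 4 and 8, anterior chamber cell relapse at 12, unsuppressed at 16 (route b) | yes | success | inflamed; efficacy failure under the rescue rule |
| Quiet at 4, relapse at 8, unsuppressed at 12, leaves the study | no | non-success | not seen |

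In route b the 4-week limit falls at week 16, so the visits are complete when failure is declared. The last record shows that the visit-completion condition already removes subjects who leave earlier.

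**Size on assumed rates.** The documents give no visit-level rates and no figure for this outcome to reproduce. Assume that all subjects are active at baseline, that an active subject becomes quiet with probability q = 0.25 to 0.40 per 4 weeks, and that a quiet subject flares with probability r = 0.05 to 0.20 per 4 weeks. The proportion quiet at successive visits is p(next) = p(1 − r) + (1 − p)q, starting from 0.

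Route a adds r × p(week 12):
- q = 0.25, r = 0.05: p runs 0.250, 0.425, 0.5475; route a = 0.05 × 0.5475 = 0.027.
- q = 0.30, r = 0.10: p runs 0.300, 0.480, 0.588; route a = 0.10 × 0.588 = 0.059.
- q = 0.40, r = 0.20: p runs 0.400, 0.560, 0.624; route a = 0.20 × 0.624 = 0.125.

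So route a adds about 3 to 12 points.

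For comparison, an unrestricted ever-quiet rule has success rate 1 − (1 − q)^4. At q = 0.30 and r = 0.10 this is 76.0%, against 65.3% quiet at week 16, a gap of 10.7 points. Over the whole range the gap is 5 to 22 points. That model ignores study exit, so it is an upper bound.

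**Effect on an arm difference, with exits applied.** Take q = 0.35 in both arms, and r = 0.05 in one and 0.20 in the other. Without exits, 76.2% v 61.0% are quiet at week 16, a difference of 15.1 points.

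*Every flare at week 8 or 12 leads to exit.* Never-flared subjects quiet at week 12 number q(1 − r)² + (1 − q)q(1 − r) + (1 − q)²q:
- r = 0.05: 0.3159 + 0.2161 + 0.1479 = 0.6799
- r = 0.20: 0.2240 + 0.1820 + 0.1479 = 0.5539

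Add those first quiet at week 16, 0.65³ × 0.35 = 0.0961. Literal success is 77.6% v 65.0%, a difference of 12.6 points. Scored on week-16 status in the same model:
- r = 0.05: 0.6799 × 0.95 + 0.0961 = 74.2%
- r = 0.20: 0.5539 × 0.80 + 0.0961 = 53.9%

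That difference is 20.3 points.

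*Every flare is anterior chamber cell and one is permitted.* Add first flares at week 12, r[q(1 − r) + (1 − q)q] = 0.0280 v 0.1015. Also add those who flared at week 8 and were quiet again at week 12, q²r = 0.0061 v 0.0245. Literal success is 81.0% v 77.6%, a difference of 3.4 points. Scored on week-16 status in the same model:
- r = 0.05: (0.6799 + 0.0061) × 0.95 + 0.0280 × 0.35 + 0.0961 = 75.8%
- r = 0.20: (0.5539 + 0.0245) × 0.80 + 0.1015 × 0.35 + 0.0961 = 59.4%

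That difference is 16.3 points.

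**The case against.** The strongest reply is that quiet eyes at week 16 were plainly intended. The objective sets week 16 as its date, visits end for subjects who have not achieved resolution by then, and the relapse clock starts at that visit and waits for a sign to appear. The article also condenses a fuller protocol. This stands as evidence of intent. It does not repair the rule, which is written out in Table 1 and repeated in Table 4 without the condition.

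Three stronger readings are tempting, and the documents do not support them:
- A reader might infer that one quiet examination at any visit is enough. It is not: all visits to week 16 must be completed, and the rescue rule removes most earlier relapsers before then.
- A reader might infer that a true arm difference could vanish. That result comes from a model without exits in which both arms have the same quieting rate, so ever-quiet rates are equal by construction. With exits, 12.6 or 3.4 points remain in the example above. A loss-of-power figure is not warranted either. The sample size was set for the primary outcome, and the Table 4 row does not say that the monotherapy arms are pooled.
- A reader might infer a contradiction with the week-16 analysis of the individual signs. That analysis records presence at a visit, while this outcome records achievement by a date. The two can differ without conflict.

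**Conclusion.** The point holds for this secondary outcome, and for the time-to-relapse analysis if entry uses the same status. As written, the rule scores as successes subjects whose signs return at week 16, and subjects with a week-12 anterior chamber cell relapse still unsuppressed at week 16. The first group alone adds about 3 to 12 points to the response rate on the assumed rates. An arm difference that comes from staying quiet is diluted by an amount that depends on how the exit rule operates. These sizes are illustrations: the rates and the all-active start are assumptions, not figures from the documents. The primary outcome is not exposed in the same way, because it requires resolution to be maintained to week 52. The text should be corrected, but the trial's main result does not turn on it.

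**What to change.** In Tables 1 and 4, define the outcome as no ocular inflammatory sign at the week-16 visit and no treatment failure of any cause, including inefficacy, up to and including week 16. Keep the taper and visit-completion conditions. Use the same week-16 status for entry to the time-to-relapse analysis.

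Reconcile the definition with Authorised rescue medication and Study procedures by stating how a permitted anterior chamber cell relapse present at week 16 is scored. Under the definition proposed here it would be a non-success for this outcome, and the text should say so openly. This concerns scoring only and leaves the clinical rule as it is.

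The cost is a short wording change and somewhat lower reported week-16 response rates. The examination is already scheduled, and neither data collection nor sample size changes.
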